#### Enrolment of the cohort

Cohorts of children aged ≥ 6 months to 9 years 11 months will be enrolled from randomly selected compounds using a master list generated during baseline mapping to achieve the desired sample size (see “Recruitment {15}”). HHs within each cluster will be identified by simple random sampling using a statistical software package such as SAS, STATA, or R. Selected HHs will be visited and all eligible children in the HH invited to participate in the study. The children will be enumerated on a tablet and a randomization program run to pick one who will be invited to participate in the study. The study will be explained and consent obtained from the child’s parent/guardian before enrolling the child in the study.

At enrolment, the age and sex of the child will be recorded and the parent/guardian will be asked about the use of ITNs and anti-malarial drugs. A fingerstick blood sample will be taken for a malaria RDT, a blood smear, and a measurement of hemoglobin. At this time, cohort participants will be presumptively cleared of parasites with a treatment dose of AL unless they have recently been treated (within the last 2 weeks) in which case, their microscopy results will be fast-tracked to confirm clearance and if not cleared, another dose of AL will be given. Children will be treated according to Rapid Diagnostic Test (RDT) result throughout the follow-up period unless the microscopy result is positive following a negative RDT or where an RDT was not done.

All enrolled children will be provided a LLIN. This will allow us to measure the added benefit of SR product above that provided by current WHO recommended malaria preventive measures. In addition, children enrolled into each baseline, cohort 1, and cohort 2 will be provided a treatment dose of AL free of charge to clear any prepatent or patent malaria parasites.

#### Cohort follow-up

Children enrolled in the baseline cohort will be followed for a 4-month period, prior to the distribution of the study products. To avoid substantial LTFU due to study fatigue, two independent cohorts (cohort 1 and cohort 2) will be recruited and followed with intervention each for 12 months (see Trial Design {8}); therefore, the total period of follow-up will be 28 months; 4-month baseline phase and 24 months after deployment of the intervention. Cohort 1 will end 12 months after the SR is deployed. Cohort 2 will be recruited, enrolled, and cleared of infection with a treatment dose of AL at enrolment as described above. Children enrolled in the baseline cohort will be eligible for inclusion in cohorts 1 or 2; however, those children enrolled in cohort 1 during intervention will not be eligible for inclusion in cohort 2. The recruitment, enrolment, screening, and follow-up of cohort 2 will be the same as described for the cohort 1.

Follow-up visits for each baseline, cohort 1, and cohort 2 will alternate between a clinic visit (monthly; passive case detection) and a home visit (every 2 weeks; active case detection). Routine blood sampling will occur at the clinic, whereas blood sampling will only occur during home visits if subjects have reported history of fever in the last 48 h. Study participants will be issued with an appointment card where all upcoming appointments will be recorded. In between the clinic appointments, community interviewers may refer participants to the clinic for additional assessment by the clinical officer using the participant referral slip. Participants will be instructed to visit a study health facility for any unscheduled sick visits, or they will be visited at their home if they cannot reach the clinic. Missed visits will be considered minor protocol deviations and will be collated and reported to KEMRI Scientific Ethical Review Unit (SERU) and UND along with the annual progress report. Three consecutive missed visits will prompt consideration for LTFU and withdrawal from the study.

At each visit, the parent/guardian will be asked about recent use of ITNs and other vector control interventions as well as recent history of child’s illness and recent use of anti-malarial drugs. At every clinic visit (on a monthly basis), a blood smear will be taken for malaria diagnosis. An RDT will be taken if the participant has a recent history of fever. At the intervening home visits, a blood sample will only be taken if the child has a recent history of fever or other symptoms attributable to malaria infection. Total blood volume for samples at each visit will not exceed 500 μL.

Cohort children who test positive for malaria by RDT will be treated with AL free of charge. Blood slides of children who test negative by RDT will be prioritized for examination, and treatment will be provided based on a single positive reading. However, the endpoint measurement for formal analysis will be based on examination of all blood slides by at least two expert microscopists with any discordant results resolved by a third. Cohort children will be provided a transport reimbursement for monthly scheduled clinic visits to offset the cost of coming to the clinic. Transport to hospital, if needed, will be facilitated through transport reimbursement. If there is illness or injury due to study products or procedures, fees will be paid for care at the government clinic or county or referral hospital. Referrals will be done using the general referral form. If the level of care necessary of the illness/injury is not available at the government hospital, the study will pay for care at a private health facility.

Cohorts will also be enrolled to estimate the diversionary effect of the SR intervention. Children in this cohort will be recruited from buffer zones surrounding each cluster. HHs in this area will not receive the SR or the placebo but recruitment, enrolment, screening, and follow-up procedures will be the same as described.

#### Entomological collections

Twenty clusters (10 SR, 10 placebo) will be randomly selected to estimate the impact of the SR on entomological measures of malaria transmission. Within each cluster, CDC light trap collections will be conducted in 10 randomly selected HHs within the core area of each sentinel cluster every month to assess the impact of intervention on the density of *Anopheles* mosquitoes indoors. On the same night, CDC light trap collections will be performed in 15 randomly selected HHs in the buffer zone of the same cluster to estimate the diversionary effect of the SR. The clusters for entomological sampling will be selected at the start of the baseline phase of the trial and will remain fixed throughout the study while within each selected cluster, HHs where CDC light trap collections will occur will be randomly selected each month.

In addition, quarterly HLCs will be conducted indoors and outdoors from a total of 48 HHs in a subset of 12 (6 SR and 6 placebo) of the 20 randomly selected clusters for measuring entomological endpoints. The 12 clusters will remain fixed throughout the study. Four HHs will be randomly selected in each of the clusters and will remain fixed throughout the follow-up period. Sampling will be performed for 2 weeks (6 nights per week) each quarter.

### Plans to promote participant retention and complete follow-up {18b}

Participant retention strategies include participant tracing when they miss appointments, visit reminders, calling participants after every 2 weeks for the home visit, during the follow-up phase, requests for participants to inform study staff of moves outside or within the study area, fostering relationships with participants as they engage in ancillary care at study clinics, provision of community interviewer and CO contact information for easy communication to alleviate concerns, and periodic generation of retention rates to evaluate strategies. A study SOP will be developed to provide more details on retention activities to be conducted by study staff.

### Data management {19}

#### Data forms

A combination of standardized paper-based or digital forms (programmed on Android tablets) will be used such that variable codes can be cross-referenced during interim and final analyses. KEMRI and the UND Center for Research Computing (CRC) will work together to develop the quantitative forms. Entered data (entomological and epidemiological) will be automatically assessed for quality using established quality control rules, then reviewed and appended to the data already present. Data forms can be made available upon request submitted to the UND Lead PI. All data issuing from the electronic data collection system will follow the same data collection processes outlined in the paragraphs below. Any changes to quantitative data forms will need to be agreed upon by the Site PI (in consultation with CDC technical advisors) and UND. In the event individuals cannot come to a consensus on proposed changes, the UND Lead PI will make the final decision.

#### Data quality control and quality assurance

Assigned data management study staff will be responsible for verifying data accuracy and assurances that data collection is following standardized protocols. This will promote data quality and that the trial is performed in compliance with GCP and the applicable regulatory requirements(s). Training of study staff on data collection will occur prior to commencement of baseline and throughout the trial period through refresher training events. Standardized data collection forms will be used and source data verification will occur through three primary mechanisms: (1) self-quality checks, making sure data forms are fully completed; (2) data queries, quality checks on a routine basis; (3) external monitoring, by fhiClinical, the clinical research organization responsible for trial oversight, to report on any irregularities that might be raised during monitoring visits. In addition, tablet-based digital forms will be used for data entry and uploading into the master database which will be custom designed to include rules and conditions for data variable responses (e.g., text responses cannot occur for numeric value, and thresholds for numeric data).

#### Data sharing policy

Using CommCare, KEMRI will collect data which will be securely stored on Android devices and then synchronized to the CommCare cloud. Data will then undergo an initial cleaning and de-identification by KEMRI, before being synced to UND’s central database. Data from KEMRI to UND will be transferred through a dedicated secure FTP server with password-protected access from KEMRI and CDC.

This project will generate considerable data and biological samples over the course of the 2-year study period. The data management plan will follow the guidelines and suggestions put forward by the National Institutes of Health in its online guidance document https://humansubjects.nih.gov/data_safety and by the respective institutions involved in the research (KEMRI, UND, and CDC), as well as by the community of interest (comprised of colleagues, scientists working in the same field, the biomedical community researching tropical parasitic diseases, and public health officials). The goal is transparent sharing of key findings and data so that the broad impacts of the research are meaningful and useful to key stakeholders and will therefore be shared with stakeholders as may be required.

Every consideration will be given to the nature of beneficence and justice expressed in the guiding documents for research on human subjects. Biological samples of mosquitoes and parasites will be maintained appropriately to avoid deterioration. These materials will be made available to researchers upon reasonable request and with the caveat that any forthcoming publications from research on the samples should consider the original researchers and their inclusion in the resulting publications when warranted.

#### Data storage

Any data collected on paper forms (including consent/assent forms) will be scanned and transferred to binders for storage in a secure and locked restricted access area, while all electronic captured data will be archived with a documented history of changes or corrections at the local study site.

A password-protected central study database warehousing data will be developed and managed by the UND CRC to serve as a data repository and utilized for safe data storage, extraction, integration, and analysis. The data warehouse and file repository will be backed up weekly at the local server level to ease recovery as needed.

In addition, data will be stored and backed up on the CommCare cloud. Access to study data is controlled through centralized administration, and access will be granted only with the UND Lead PI’s permission. Research records for all study subjects including history and physical findings, laboratory data, and results of consultations are to be maintained by the local Site PI in a secure storage facility at KEMRI, for a minimum of 3 years after the end of the project or until notified by grantee.

### Confidentiality {27}

Any participant information will be confidential. The results of this study will be made available to sponsors of this study but personal information will not be provided to anyone. The UND CRC will not share identifiers, but instead use a code. The code will be kept by the UND CRC, and securely at the KEMRI site according to site-specific IRB specifications and requirements for emergency situations. Raw data will be anonymized and GPS tag-blurred to remove sensitive information prior to sharing to other study sites or outside of the core study team according to local IRB requirements.

A Privacy Impact Assessment will be developed for the project, and a set of protocols and contingency plans for emergency paper-based and digital data destruction will be developed in order to guarantee privacy of research subjects in case of unforeseen risks.

### Plans for collection, laboratory evaluation, and storage of biological specimens for genetic or molecular analysis in this trial/future use {33}

This study does not include genetic or molecular analyses. Standardized protocols will be developed for the collection, storage, use, and eventual destruction of blood samples collected as part of the trial.

## Statistical methods

### Statistical methods for primary and secondary outcomes {20a}

#### Primary hypothesis

H_0_: SR does not reduce the first-time malaria hazard rate compared to placebo in Kenya.

H_1_: SR reduces the first-time malaria hazard rate compared to placebo (first-time malaria hazard ratio between SR and placebo is < 1; the expected hazard ratio is 70% or PE is 30%.

#### Secondary hypothesis

H_0_: SR does not reduce the overall malaria hazard rate compared to placebo in Kenya.

H_1_: SR reduces the overall malaria hazard rate compared to placebo (overall malaria hazard ratio between SR and placebo is < 1; the expected hazard ratio is 70% or PE is 30%).

#### Population for analysis

The intention to treat (ITT) analysis is the primary analysis approach for both the primary and secondary objectives. The ITT population includes the first recruited participant from each recruited HH that received at least one SR product or placebo according to the cluster randomization schedule. The per-protocol analysis is included as a supplementary analysis for the primary and secondary objectives. The per-protocol population includes the participants from the ITT population that are treated following the specifications of the study protocol without major protocol deviations.

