### Objectives {7}

The study’s primary objective is to demonstrate and quantify the protective efficacy (PE) of the Mosquito Shield™, a transfluthrin-based SR product, in reducing the incidence of malaria infection in humans.

Secondary objectives will address issues related to the optimization and application of SR products for public health and confirm the range of contexts within which SR PE can be achieved. Secondary objectives are:
To estimate the total number of infections averted due the SR intervention by comparing the number of infections per person per year in intervention and control arms over the 2-year follow-up period;To investigate whether the SR intervention induces diversion of mosquitoes from within intervention areas to locally unprotected individuals thereby having a differential impact on infection incidence among protected and locally unprotected individuals;To measure the impact of the SR intervention on entomological correlates of transmission (e.g., vector densities, mosquito infection, host seeking/biting and parity rates) to set benchmark thresholds and streamline future intervention trials with other SR products by measuring those endpoints correlated to PE.

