### Who will take informed consent? {26a}

Informed consent will occur for three major study activities: (1) malaria incidence follow-up, (2) product application inside homes, and (3) mosquito collections. The study will be explained in local dialects (Teso and Kiswahili), and time allocated for questions to be answered. Once all concerns are addressed, ICFs will be signed.

For consent to malaria incidence follow-up, the study will first be verbally explained to the head of compounds and HHs during which their permission will be sought to list and randomize eligible children in the compound. A single child from the master randomization list will be recruited, and an ICF will be read to the parent/guardian of the child to undergo screening for enrolment. An attempt to obtain written, informed consent from both parents of the child will be made, but consent from only one parent will be required for participation. Parent(s)/guardian(s) who cannot sign their names will provide a thumb print on the ICF for documentation of willingness to participate, and a witness not associated with the study will sign the ICF indicating the form was read, and that participation and thumb-printing were given willingly without coercion. Time will be granted to those parent(s)/guardian(s) who would wish to make consultations with their family members before signing. It will be stressed to all parents/guardians approached that their children’s entry into the study is voluntary and they may withdraw from the study at any time for any reason without any penalty. In HHs with multiple children meeting the study inclusion criteria, only one eligible child will be invited to participate. Consented subjects will be assigned a subject identity code on enrolment. Consented participants will be screened for inclusion/exclusion criteria.

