### Outcomes {12}

The primary outcome measure of this cRCT will be the first-time malaria incidence rate as measured by microscopy in children aged ≥ 6 months to 10 years.

Secondary outcome measures include:
Overall new *Plasmodium falciparum* malaria infections, as measured by microscopy;The first-time and overall *P. falciparum* malaria infections in buffer zones, as measured by microscopy;The first-time and overall *P. falciparum* malaria infections by two age groups (≤ 59 months old; 5 years old to 9 years and 11 months old), as measured by microscopy;Anopheline-human contact (indoor and outdoor) using human biting rate (HBR) as an indicator for all anophelines and by anopheline species, as measured by HLC during 12-h intervals on a quarterly basis;Anopheline survival and population age structure using parity rate as an indicator for all anopheline and by anopheline species, as measured by mosquito ovarian dissections from a sub-sample of anophelines collected during HLC procedures;Anopheline infectivity using sporozoite rate as an indicator for all anopheline and by anopheline species, as measured by laboratory detection of sporozoites in mosquito heads and thoraces from a sub-sample of anophelines collected during HLC and/or CDC light trap collections;Entomological inoculation rate (EIR) as an indicator of transmission intensity for all anophelines and by anopheline species, as measured by calculating the number of sporozoite-infected anopheline mosquitoes captured per person from CDC light trap and/or HLC collections;CDC light trap indoor density for all anophelines and by anopheline species, as measured by light trap collections during 12-h intervals on a monthly basis;Insecticide resistance, as measured by WHO filter paper test and CDC bottle assays during baseline and intervention phase.Adverse events (AEs) and serious adverse events (SAEs), as measured by solicited and unsolicited reports during baseline and intervention phase. Mean, minimum, and maximum frequency and percentage of AEs and SAEs across clusters among enrolled subjects will be summarized by treatment arm.

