### Implementation {16c}

The distribution of the intervention will occur after the completion of baseline phase analyses and verification of underlying assumptions on study power (incidence, CV).

All consented HHs located within cluster core areas, including those that do not have a child subject enrolled in an incidence cohort, will have product placed inside their homes at the manufacturer’s recommended application rate of 2 units per 9 m^2^ floor area. Trained study teams will be responsible for managing product implementation including initial deployment of product, subsequent removal, and replacement at 4-week intervals.

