#### Description of study clusters

The unit of randomization for the intervention will be a cluster. A total of 60 clusters will be delineated for the trial (Fig. 1). A cluster is defined as a core area, where the SR or placebo will be implemented, plus an untreated buffer zone where diversionary effects of the Mosquito Shield™ will be measured. The core areas of each cluster will be discrete villages. In the Health and Demographic Surveillance System maintained by KEMRI and CDC in neighboring Siaya County, the average village has 103 compounds in an area of 1.75 km^2^. Compounds are defined as family units with one or more structures plus surrounding farmland. A typical family compound has 5.5 HH members. Therefore, an average population size for a village in this area is estimated to be 567 inhabitants. Pre-trial census data will be used to delineate cluster boundaries based on number of HHs and inhabitant age groups such that each cluster will have at least one anticipated child meeting the inclusion criteria for assurances of sample size requirements.

For the buffer zones, mapping will extend approximately 300–500 m from the border of each cluster core area. Assuming core areas are approximately round with an area of 1.75 km^2^, this will result in a radius of 0.75 km. Extending a buffer zone 300 m around the core area will result in a radius of 1.05 km, and extending a buffer zone 500 m will result in a radius of 1.25 km. Estimating the total area including the buffer zones and then subtracting out the area of the core area results in areas of 1.7 km^2^ and 3.1 km^2^ for buffer zones of 300 m and 500 m respectively. Typically, HHs are randomly distributed in the landscape of western Kenya and it is therefore expected that a 300 m buffer zone of 1.7 km^2^ should have a similar number of HHs as the core areas which are estimated to have an area of 1.75 km^2^. Final determination of the buffer zones will be based on mapping and the actual number of HHs required to meet the sample size of 40 HHs per cluster for the analysis of SR diversionary effects. Because the buffer zones will extend into neighboring villages, we will map approximately 100–150 villages and then select villages as core areas based on feasibility of including a 300–500 m buffer around 60 of them.

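### The population labelled ITT depends on product receipt, so it is a modified ITT set, and as worded it contradicts the buffer-zone diversion objective

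*Protocol article*

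**What the plan says.** Population for analysis makes the ITT analysis "the primary analysis approach for both the primary and secondary objectives" and then defines the set: "The ITT population includes the first recruited participant from each recruited HH that received at least one SR product or placebo". The per-protocol set is drawn from within it. The sections on the primary endpoint and on overall infections both name the ITT population.

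Consent is split by activity: "Informed consent will occur for three major study activities: (1) malaria incidence follow-up, (2) product application inside homes, and (3) mosquito collections". A parent or guardian consents to a child's follow-up; the household head or spouse consents to product in the home. Under Implementation {16c}, product goes to "All consented HHs located within cluster core areas, including those that do not have a child subject enrolled in an incidence cohort".

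Diversion is a listed secondary objective: "To investigate whether the SR intervention induces diversion of mosquitoes from within intervention areas to locally unprotected individuals". The secondary outcomes include first-time and overall "malaria infections in buffer zones, as measured by microscopy". Description of study clusters defines a cluster as a treated core "plus an untreated buffer zone where diversionary effects of the Mosquito Shield™ will be measured", and Cohort follow-up says of the buffer zones: "HHs in this area will not receive the SR or the placebo".

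**The concern.** An intention-to-treat set should be fixed by the randomised assignment. Here membership also turns on something that happens afterwards, namely whether a product was installed at least once. Children who are enrolled and followed, but live in homes that declined, would leave the primary comparison. The estimate would then describe households that accepted the product rather than treated villages as a whole. The product is deployed village-wide and the results are meant to inform policy, so children in declining homes belong in the effect of interest.

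The second problem is internal consistency. One definition is assigned to the secondary objectives without exception, yet it cannot hold for the objective studied in households that are untreated by design. Whether nearby non-users are harmed is a stated purpose of the trial (Background and rationale), so the set that answers this should not be left to interpretation.

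**Working it through.** The point rests on definitions; the only arithmetic is counting.

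**Order of events in the core area**
- Clusters are allocated before cohort 1 participants are enrolled (Sequence generation {16a}).
- Product is distributed after the baseline analyses (Implementation {16c}), so receipt comes after allocation.
- Product consent and follow-up consent are separate and may come from different adults (Who will take informed consent? {26a}).
- Table 2 does not make acceptance of product an eligibility criterion.

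An enrolled core child in a household that never received product is therefore possible, and the definition removes that child.

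**Counts, reproducing Table 1 first**
- Core, per intervention cohort: 14 × 60 = 840
- Buffer, per intervention cohort: 20 × 60 = 1200
- Sum: 840 + 1200 = 2040, as stated; three cohorts give 3 × 2040 = 6120, as in the Abstract
- Two intervention cohorts: core 2 × 840 = 1680; buffer 2 × 1200 = 2400; total 4080

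**Core children removed by the definition**

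The share of recruited households that never receive product is not given. Over an assumed range:

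| Never receiving (assumed) | Children removed of 1680 |
|---|---|
| 0% | 0 |
| 2% | 33.6, about 34 |
| 5% | 84 |
| 10% | 168 |

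The nearest indication is in Human behavior adjusted PE analysis, which expects the application rate in each household to be near 100%. That concerns application within households rather than the share that ever accept, but it points to the low end.

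**Buffer children who qualify**
- The condition is at least one product or placebo received; buffer households receive neither.
- Literal result: 0 of 2400, that is 0 of 1200 per cohort. The 2400 are 2400/4080 = 58.8% of children enrolled under intervention.
- The per-protocol set is a subset of ITT, so it holds none of them either.
- The Diversion effect section names no other population.

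**Dilution if non-receivers are kept**

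Take the planned PE of 30% among receivers and assume no benefit in declining homes. The average PE is then roughly 30% × (1 − share): 30% × 0.95 = 28.5% at 5%, and 30% × 0.90 = 27% at 10%. This is a simple average, shown only for scale.

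**The case against.** The strongest reply is that neither part changes the result much. Participants and staff are blinded, the placebo is matched in design and packaging, and analysis still follows the cluster's assignment. A decision to accept a first product cannot depend on a known arm. This stands, and it limits the core issue to a mislabelled set with a slightly narrower target population.

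Three stronger readings are tempting, and the documents do not support them.

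- **Randomisation is lost.** Enrolment itself follows cluster allocation, so a set of all enrolled children also relies on blinding for comparability. The receipt condition adds a further post-allocation selection, but it does not turn a sound comparison into an unsound one.
- **Imbalance grows in year 2, once households know the product or have had irritation from it.** The condition is at least one product ever. Every consenting core household is offered product, with or without a cohort child, so a household that used it in year 1 and refused later stays in the set. The adverse event section says only that mild, usually transient irritation is possible.
- **The diversion analysis would be run on nobody.** The sample size section sizes a buffer sample, Cohort follow-up enrols it, and the Diversion effect section models each buffer household's distance from the core and compares buffer zones by arm. The intended set is plain.

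A related defence is that the consent section makes all households in selected clusters eligible for product, and a cluster includes its buffer. The sections on implementation, cluster description and cohort follow-up rule that out.

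It can also be said that a separate diversion population is normally left to the SAP. That would answer an omission. Here the article states a rule, applies it to the secondary objectives, and contradicts it elsewhere.

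**Conclusion.** The point holds as a fault of definition and label. The set called ITT is a modified ITT set restricted to treated households, and it would drop enrolled core children whose households never received product. The number is unknown: 0 to 168 of 1680 if 0 to 10% never receive, a range that is assumed. With application expected near 100% and allocation blinded, any bias in the primary estimate is probably small.

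Assigning the same set to the secondary objectives contradicts the diversion objective. The figure of 0 of 2400 measures the contradiction on a literal reading; it does not forecast lost data. The wording should be corrected before the analysis, but this alone does not threaten the trial's conclusions.

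**What to change.** Replace the single definition with two sets, both analysed by the cluster's randomised arm:

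- **Core ITT:** every enrolled core-area child, one per household, whether or not product was accepted, installed or replaced. Use it for the first-time and overall infection analyses.
- **Diversion set:** every enrolled buffer-zone child. Name it in the Diversion effect section.

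Move the receipt condition, for core households only, to the per-protocol set, or keep it as a supplementary set labelled modified ITT. Report by arm how many enrolled core children live in households that never received product.

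The change is to wording only, since these children are already enrolled and followed. The downside is slight dilution of the estimated effect if some households decline.
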